#### 2.3.3 Arm 3—active control (stretching and toning exercises)

Participants in the active control intervention perform three training sessions per week of 60 min each. Each session starts with a 5-min warm-up, followed by a training session that includes muscle toning, balance, and body stretching exercises (light intensity). The proposed exercises were selected from a panel of 30 exercises including balance and muscle-toning exercises, yoga and Pilates sequences. To diversify, muscle-toning exercises might be performed with dumbbells and resistance bands. The intensity of stretching and toning sessions is monitored with a heart rate chest strap and should not exceed the light intensity zone defined by the ACSM (64% of HRmax or less, and a Perceived Exertion lower than 11 on the 6–20 Borg scale).

#### 2.3.4 Home-based training sessions

To remotely conduct their training on the dedicated app and website, participants who want to perform home-based training sessions are required to possess a smartphone, a computer, or a tablet connected to the internet. At the beginning of each month, training sessions at home are scheduled with the kinesiologist and the cognitive training coordinator (for the combined group). Home-based training sessions respect the guidelines of the ACTIONcardioRisk training programs highlighted above. During the first in-person training sessions at the EPIC Center, participants are trained to read heart rate monitors and recognize their perceived effort using the Borg scale. Participants are also trained to master RE and stretching movements and postures and to perform them properly without supervision. A heart rate monitor belt is lent to the participants for the intervention duration to collect continuous heart rate, energy expenditure, and the duration of physical exercise sessions. If the participants are considered sufficiently autonomous by their kinesiologist, they will be allowed to perform all training sessions from home. The compliance of the home-based cognitive training and physical exercise with ACTIONcardioRisk guidelines will be monitored on a weekly basis by the training coordinators on the dedicated app and website. In the multidomain arm, the participants performing strategy-based cognitive training sessions from home will be able to join the group session using a videoconference program. A weekly verification of the execution of the computerized cognitive training sessions is carried out by a research assistant, and a phone follow-up is conducted with the participant as needed. The kinesiologist will check the recorded physical activity training data regularly and a telephone contact is made if they do not adhere to the training program or if changes to the training program need to be implemented.

### 2.4 Outcomes

Information concerning demographics, chronic diseases, comorbidities, medications, medical history as well as anthropometric measurements (e.g., height, weight, waist circumference) are collected during a medical examination at baseline. The study physician will also monitor clinical outcomes at T0 and T2. At each timepoint, the neurocognitive functioning of participants will be assessed using cognitive tests (neuropsychological tests and computerized cognitive tasks) and the cerebrovascular functioning and structural brain imaging will be assessed through neuroimaging approaches (MRI, functional Near-Infrared Spectroscopy – fNIRS, and transcranial Doppler – TCD) before and after the intervention. A comprehensive assessment of physical functioning and body composition (cardiorespiratory fitness, mobility, balance, muscular strength, bioelectrical impedance analysis), cardiovascular and metabolic functions (arterial stiffness and endothelial function, blood draws), biological markers, and self-reported mood, anxiety, and health-related quality of life, will also be performed. All assessments are synthesized in Table 2.

**TABLE 2 T2:** Schedule of assessments.

	Preliminary call	First visit	12 months																		
			Pre-training assessments (T0)							Mid-training assessments (T6)					Post-training assessments (T12)						
**Session**	A	B	1	2	3	4	5	6	7	1	2	3	4	5	1	2	3	4	5	6	7
**Duration (min)**	45	90	125	110	90	110	125	60	150	95	110	120	105	35	95	110	120	105	125	60	150
**Procedure**																					
Consent form	x																				
PARQ +	x																				
Blood draw				x							x					x					
Cortisol		***^2^**								***^2^**					***^2^**						
Gut microbiome		x													***^3^**						
Accelerometry		x																			
Medical evaluation			x																		
Hearing assessment			x																		
Questionnaires			***^1^**							***^1^**					***^1^**						
**Cognition**																					
MMSE		x																			
MOCA		x									x					x					
Paper-pencil Assessments				x							x					x					
Computerized tasks 1			x							x					x						
Computerized tasks 2						x							x					x			
Computerized tasks 3							x							x					x		
**Functional status**																					
Mobility		x										x					x				
Functional		x										x					x				
Anthropometric measures			x							x					x						
VO2 max			x							x					x						
**Cardiovascular health**																					
Flow-mediated dilation									x												x
Central artery stiffness									x												x
Vascular reactivity									x												x
**Neuroimaging**																					
MRI							x	x											x	x	
Spectroscopy					x							x					x				
Transcranial Doppler (TCD)						x							x					x			

*_1_Questionnaires will always be given on the first session of every testing period.

*_2_Cortisol material will be given at the first visit and on the first session of T6 and T12 testing periods.

*_3_Gut microbiome material will be given on the first session of T12 testing.

#### 2.4.1 Primary outcome—cognition

Cognitive functioning is assessed using a battery of validated paper-pencil and interview-based neuropsychological assessments and computerized cognitive tasks. All assessments are performed under the supervision of a neuropsychologist or a trained psychology student. The neuropsychological tests are administered in a fixed order: MoCA (Nasreddine et al., 2005), Rey auditory verbal learning test—RAVLT (Lezak et al., 2012), Digit Symbol Substitution Test—DSST (Jaeger, 2018), Stroop Color-Word Interference Test—SCWIT (Jensen and Rohwer, 1999), Phonological and Semantic Fluency from the D-KEFS battery (Letters P, T, L – 60 s maximum) (Delis et al., 2001), Trail Making Test—TMT A and B (Tombaugh, 2004), Digit Span and Similarities subtest from the WAIS-IV (Wechsler, 2008). All the above tests are validated and normalized for an older adult population (Lezak et al., 2012; Strauss et al., 2006).

First, the Montreal Cognitive Assessment (MoCA) score will measure global cognition (Nasreddine et al., 2005). Then, the executive functions, processing speed, and episodic memory will be assessed by three composite Z-scores calculated from specific components of the neuropsychological tests, as it has already been done in the past (Desjardins-Crépeau et al., 2014). The composite Z-scores will be computed by averaging the Z-scores of tests and sub-tests assessing the same cognitive functions. The processing speed score includes: DSST score, time to complete SCWIT naming and reading conditions, and time to complete TMT part A. The executive score includes time to complete inhibition and switching conditions of the SCWIT, and time to complete part B of the TMT. The memory score includes the following components from the RAVLT: total number of words recalled in 5 trials, immediate recall after interference, delayed recall, recognition, and false recognitions. Their internal consistency will then be verified using Cronbach’s alpha (Ferketich, 1990).

Computerized cognitive tasks are also completed, including a dual-task (Lussier et al., 2020), a Stroop task (Saillant et al., 2021), and an N-back task (Boujut et al., 2020). The response time to the computerized tasks is recorded in milliseconds. Subcomponents of each computerized task will allow for the dissociation of attentional control mechanisms from processing speed. To minimize practice effects, a trained and a transfer version (i.e., using different stimuli) of each computerized task is presented in a counterbalanced order between the participants via a Latin square procedure. Previous studies have validated this approach and showed that cognitive-training improvements can be detected through the transfer task (Vrinceanu et al., 2022). The participant’s equipment (i.e., computer or tablet) for the computerized tasks is documented, and participants must use the same equipment across all testing sessions.

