#### 2.3.2 Arm 2—multidomain intervention (combined cognitive training with aerobic and resistance exercises)

The multidomain intervention involves an identical physical exercise program described in the previous section in addition to cognitive training. The cognitive training component takes place before each physical exercise session. Three sessions of 30 min are scheduled each week, including one group session and two individual computerized cognitive sessions. The group session, which takes place once a week, uses strategy-based training adapted from the MEMO + program (Belleville et al., 2018). This group program covers interactive educational lessons on age-related changes in memory and attention and teaches participants different mnemotechnic strategies aimed at improving memory (e.g., face-name association, visual imaging). Some sessions of the group program also aim to help the development of strategies to manage multiple aspects of their daily life, such as anxiety, sleep, and nutrition. The remaining two individual computerized cognitive training sessions focus on the following three components: (a) dual-task training that requires participants to share attention between two concurrent tasks and to maintain and prepare for many alternative responses (i.e., Dual-task) (Lussier et al., 2020); (b) working memory training, which involves the maintenance and constant updating of information in working memory while recalling items presented earlier (i.e., N-Back task) (Boujut et al., 2020); and (c) inhibition and switching training requiring the participants to refrain from giving an automatic response and alternate between following different rules (i.e., Stroop task) (Saillant et al., 2021). During each individual session, participants perform only two of the three different visuomotor tasks (15 min each), each with their respective sets of visual stimuli (e.g., letters, numbers, animals) and matching hand-button symbols. The level of difficulty of each cognitive task is gradually increased over the weeks of intervention to avoid cognitive task automatization and maintain stimulation (Flegal et al., 2019). Participants are instructed to perform as fast as possible while maintaining accuracy. The training also includes online feedback and a histogram of daily performance to encourage improvement. The three tasks will be presented in a fixed order for all participants.

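### Two of the three parts of the primary executive score use the Stroop paradigm that only the multidomain arm trains, so a Stroop-specific gain would count as a general executive benefit

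*Protocol article*

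**What the plan says.** **The outcome.** Section 2.4.1 of the protocol article builds three composites beside the MoCA. For executive function: "The executive score includes time to complete inhibition and switching conditions of the SCWIT, and time to complete part B of the TMT". On weighting: "The composite Z-scores will be computed by averaging the Z-scores of tests and sub-tests assessing the same cognitive functions". Phonological and semantic fluency and Digit Span are also administered but enter none of the listed composites.

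**The training.** Section 2.3.2 states: "The multidomain intervention involves an identical physical exercise program described in the previous section in addition to cognitive training". The cognitive part has three weekly sessions, "including one group session and two individual computerized cognitive sessions". One of the three computerized components is "c) inhibition and switching training requiring the participants to refrain from giving an automatic response and alternate between following different rules (i.e., Stroop task"). Difficulty rises over the weeks, participants are told to respond fast, and they receive feedback. Sections 2.3.1 and 2.3.3 describe no cognitive training for the exercise and control arms.

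**The safeguard.** For the computerized tasks, section 2.4.1 provides that "a trained and a transfer version (i.e., using different stimuli) of each computerized task is presented in a counterbalanced order", with the stated aim of limiting practice effects. Section 2.12 analyses those tasks apart from the four primary measures.

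**The claim.** Section 1.2 hypothesises that the multidomain arm will outperform the other two arms on executive functions, among other domains. Section 2.12 tests each of the four measures at 0.0125.

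**The concern.** Training exposure to the Stroop paradigm differs by arm and is present only in the arm expected to win. The executive composite weights that paradigm at two thirds. If a year of inhibition and switching practice makes participants faster on Stroop-type tasks and on nothing else, the composite still rises and the measure can still pass its test. The stated hypothesis concerns executive functions in general, which is a broader claim.

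The authors separate trained from transfer performance for the computerized tasks, but the article draws no such distinction for the score that carries the primary claim. At stake is what a positive executive result would mean, against exercise alone as well as against control.

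**Working it through.** **1. The plan's own figure (section 2.6).** Difference 0.425 − 0.239 = 0.186; SD 0.298; standardised effect 0.186/0.298 = 0.624. A two-sided two-sample t-test at 0.05 has power 0.807 with 42 per group and 0.797 with 41, so 42 reproduces. Attrition of 20%: 42/0.80 = 52.5, rounded up to 53; 3 × 53 = 159. At the 0.0125 level of section 2.12 the same effect with 42 per arm has power 0.62, which serves below as a benchmark.

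**2. Weight of the Stroop.** Executive score = (inhibition z + switching z + TMT-B z)/3. The SCWIT share is 2/3.

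**3. Training dose in the multidomain arm.** Inputs: 46 weeks (section 2.3), two individual sessions a week, and two 15-minute tasks out of three per session (section 2.3.2: "During each individual session, participants perform only two of the three different visuomotor tasks (15 min each").
- 46 × 2 × 2/3 = 61.3 blocks
- 61.3 × 15 min = 920 min = 15.3 hours, or 20 min a week

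Even rotation of the three tasks is an assumption. The dose in the other two arms is zero.

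**4. Effect of a Stroop-only gain.** Let both SCWIT z-scores improve by g SD in the multidomain arm and TMT-B not at all, with z-scores oriented so that higher is better.
- Shift of the composite = (g + g + 0)/3 = 2g/3
- SD of the composite = √((3 + 6ρ)/9), where ρ is the correlation between components (assumed): 0.73 at ρ = 0.3, 0.82 at 0.5, 0.89 at 0.7
- Standardised effect d = (2g/3)/SD

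Setting d = 0.624 gives g = 0.624 × SD × 3/2 = 0.68, 0.76 and 0.84 for ρ = 0.3, 0.5 and 0.7.

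**5. Chance of a significant result** (noncentral t, two-sided 0.0125, 42 per arm, noncentrality d√(42/2), 82 df):

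| g (SD) | shift 2g/3 | ρ = 0.3 | ρ = 0.5 | ρ = 0.7 |
|---|---|---|---|---|
| 0 | 0 | 0.0125 | 0.0125 | 0.0125 |
| 0.2 | 0.133 | 0.047 | 0.040 | 0.035 |
| 0.3 | 0.200 | 0.103 | 0.081 | 0.068 |
| 0.5 | 0.333 | 0.328 | 0.254 | 0.205 |
| 0.8 | 0.533 | 0.784 | 0.670 | 0.573 |

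Neither g nor ρ is in the document, so the table is an illustration. It also uses a simple comparison at one time point. A mixed model that exploits the baseline could have a smaller error SD, and the same g would then be detected more often.

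**The case against.** **The trained task is not the outcome test.** A reader might infer that the multidomain arm rehearses the primary test for a year. The document does not support that. Section 2.3.2 describes visuomotor tasks with their own stimuli and button responses, while Table 2 schedules the paper-pencil assessments separately from the computerized tasks. What is shared is the paradigm and its two conditions. Nor are the other arms without any Stroop exposure: everyone meets Stroop tasks at assessments. That exposure is common to all arms and does not bias the comparison; the training exposure does differ. This objection stands, and it makes an SCWIT gain near transfer.

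**A small gain would not do it.** A reader might reason that 0.186 × 3/2 = 0.279, so a Stroop-only gain of about 0.28 SD reproduces the whole planned difference. That mixes scales. The 0.186 is paired with an SD of 0.298, whereas an average of three unit-variance z-scores has an SD of about 0.73 to 0.89. On that scale a gain of 0.279 gives d of 0.186/0.89 to 0.186/0.73, about 0.21 to 0.26, significant at 0.0125 only about 6% to 9% of the time.

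**A structural separation exists.** The trained computerized tasks are kept out of the primary composites, and by section 2.4.1's notion of transfer (different stimuli) the SCWIT already counts as a transfer measure. Improving inhibition is also what the training is for. This is fair, but it supports a conclusion about Stroop-type performance and does not separate that from executive function in general.

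**Precedent and the unseen SAP.** The composite follows earlier scoring, leaving out fluency and Digit Span is a choice and not an error, and a sensitivity analysis may sit in a SAP that is not shown. Precedent does not cover a trial in which one arm alone trains on the score's main component. The score's content and the trained task are both fixed in this article, so the overlap can be judged from it.

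**Conclusion.** The concern holds as a limit on interpretation of one of the four primary measures. Two thirds of the executive score rests on a paradigm trained only in the hypothesised arm, for about 15 hours under even rotation, and a gain confined to that paradigm would be scored as an executive benefit. The direction of any such effect is fixed; its size is unknown.

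A Stroop-only gain would need to be about 0.68 to 0.84 SD to match the planned standardised effect (assumed ρ of 0.3 to 0.7). At 0.5 SD the chance of significance is about 0.21 to 0.33, against 0.0125 with no gain.

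The document does not show that such a gain will occur, and the other measures are not undermined in the same way. The MoCA is untouched by this argument, and the memory score comes from the RAVLT alone. The processing speed score includes SCWIT naming and reading times, so a smaller overlap may exist there.

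**What to change.** Keep the primary composite. In section 2.12:

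- Pre-specify a supportive executive analysis without the SCWIT, built from phonological and semantic fluency and TMT-B and fitted with the same mixed model. Leave Digit Span out, because it overlaps with the N-back training. State that TMT-B shares the switching demand, which makes fluency the cleaner element.
- Report its estimate and confidence interval beside the SCWIT inhibition and switching results, shown separately and labelled near transfer.
- State in advance that, if the effect is confined to the SCWIT, the conclusion is limited to near transfer on Stroop-type tasks. A rule requiring only the same direction would be too weak, since with no transfer it is met about half the time.

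The cost is one further pre-specified analysis on tests already given, with no new testing and no change to the primary outcome. The downside is that the supportive score covers a somewhat different mix of executive abilities and is not separately powered, so its interval should be read for compatibility with a general benefit and not as a second test. Table 1 lists the trial as recruiting, so the change can be fixed before unblinded results are seen.

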#### 2.4.2 Secondary outcome—neuroimaging

The neuroimaging data will be extracted from an MRI scan, a combined NIRS/TCD recording, and an fNIRS recording. The secondary variables of interest are (1) cerebral autoregulation of the frontal cortical region and of the middle cerebral artery (NIRS/TCD + plethysmography), (2) cerebral vasoreactivity of the whole brain (MRI), (3) cerebral vasoreactivity of the prefrontal cortex and of the middle cerebral arteries (NIRS/TCD), (4) cerebral pulsatility of the prefrontal cortex and the middle cerebral arteries (TCD), (5) cerebral activity (fNIRS), (6) brain morphology (structural MRI), and (7) changes in brain small vessel disease (pathological MRI).

##### 2.4.2.1 Magnetic resonance imaging

The MRI recording (Table 3) is made over two separate visits using a Siemens 3T Skyra MRI scanner equipped with a 32-channel array coil. The recording combines anatomical MRI and arterial spin labeling (ASL) MRI to assess cerebrovascular reactivity. In addition, structural markers of cerebral microangiopathy standardly used in the literature are also recorded (e.g., lacunes, microbleeds, white matter hyperintensities). To do so, multi-contrast MRI (T1w, T2w, FLAIR, susceptibility) is acquired in compliance with the STandards for ReportIng Vascular changes on nEuroimaging (STRIVE) (Wardlaw et al., 2013).

**TABLE 3 T3:** MRI acquisition sequences.

Sequence	Resolution	Scan duration	Purpose
T1 MP-RAGE	1 × 1 × 1 mm	7 min	Morphometry, Gray/White matter segmentation
T2 TSE	1 × 1 × 1 mm	4 min	lacunes, perivascular spaces, old infarcts
T2 SWI	1 × 1 × 3 mm	4 min	Microbleeds
DTI	2 × 2 × 2 mm, 64 dirs	14 min	Recent white matter lesions, fractional anisotropy, connectome
ASL Hypercapnia	4 × 4 × 4 mm. TR = 4 s	14 min	Vasoreactivity: variations of CBF induced by hypercapnia

For the breathing manipulation during MRI ASL hypercapnia, the participant will be asked to breathe three pre-mixed gases: a hypercapnic mixture (5% CO_2_, 21%O_2_, and 74% N_2_), a hyperoxic mixture (75%O_2_ and 25% N_2_) and carbogen (5% CO_2_ and 95%O_2_). Participants will be asked to breathe each gas for 2 min, preceded and followed by 2 min of air breathing. The participant will wear a re-breathing face mask connected to an automated gas delivery system. The mask has a sealing contour to prevent leakage and mixture with outside air. The flow rate will be set at 20 L/min. End-tidal CO_2_ and O_2_ concentrations will be measured using the Thornhill Respiract gas monitoring equipment. The participant will be asked to try to mask outside the MRI machine before the beginning of acquisitions to ensure the comfort of the breathing manipulation. Comfort will be assessed using the scale dyspnea scale by Banzett et al. (2015). Participants reporting a discomfort rating of 5 or above will be excluded from this sequence.

##### 2.4.2.2 Near infrared spectroscopy/transcranial Doppler combined recording

A combined NIRS/TCD assessment is used to record cerebral autoregulation and pulsatility. The cerebral autoregulation assessment involves the participant resting in a supine position for 5 min, then standing up for 5 min, while undergoing simultaneous recordings of TCD, NIRS, ECG and continuous arterial blood pressure (finger plethysmograph, Finapres NOVA). For the NIRS/TCD cerebrovascular reactivity measure, the participant is asked to breathe a controlled gas mixture through a mouthpiece, alternating between room air and a hypercapnic mixture (5% CO_2_, 21% O_2_, and 74% N_2_). The session lasts 12 min with alternating 2-min blocks of normal and hypercapnic conditions. While the TCD signal is recorded, the end-tidal O_2_ and CO_2_ concentrations are tracked by a gas analyzer (Gemini O_2_/CO_2_ monitor). Hypercapnic blocks are manually administered by opening/closing a pre-mixed gas cylinder. The values obtained will be related to CVR measures obtained by MRI as a multimodal bridge. The NIRS/TCD system is also employed to assess the regulation of CBF with respect to variations of blood pressure (commonly referred to as static cerebral autoregulation (Donnelly et al., 2015), and the pulsatility that reflects arterial elasticity (Tan et al., 2017). During the NIRS/TCD procedure, a concurrent electro-cardiogram (GE TRAM 3-leads ECG or Finapres NOVA 3-leads ECG add-on) is also recorded to identify cardiac cycles. These cycles are then used to extract diastole and systole amplitudes and compute pulsatility indexes from both NIRS and TCD traces.

